## Multicenter Studies

As stated in the protocol, centers with less than 20 subjects will be pooled with larger centers within the same geographic region so that centers are of a reasonable size for the purpose of the statistical analyses. This process will be performed and finalized before the treatment codes are unblinded.

In multicenter randomized controlled clinical study, there were some difference effect in different center due to different baseline, clinical practice or other factor, therefore, central effect analysis was required. Stratified analysis was used to exclude the mixed effect of results caused by

Version 1.0

Jan 09 2019

center effect: each center was served as a stratum, calculating the HR by Cox proportional hazards model.

### Examination of Subgroups

The rate of new stroke (ischemic or hemorrhagic) at 90 days will be presented for each level of the covariates listed below. The extent to which the treatment effect varies across levels of each subgroup will be assessed through interaction tests.

### Multiple Comparisons and Multiplicity

A single primary efficacy variable has been defined for this study, with all other efficacy variables identified as secondary or other. Similarly, only one treatment comparison is of interest in the study and therefore there are no requirements to adjust for multiple comparisons or multiple endpoints within this study.

## 10. Data handling conventions

### Premature Withdrawal and Missing Data

If any subject withdraws prematurely from the study (prior to the final visit D90±7 days assessment), they are required to complete the withdrawal visit in the CRF. The reasons for withdrawal will be presented in a summary table. For the purposes of summaries and analysis of clinic visit data, this visit will be assigned to the next scheduled clinic visit for that subject, regardless of whether the date falls within the next visit window.

Subjects who withdraw before the end of the study, but who do provide at least one post-baseline measure for a particular endpoint, will be included in the analysis.

Subjects who do not attend any visits after randomization will be excluded from analysis of any endpoint, as no post-baseline data will be available.

## Event Rates

The number of people and person-time of events should be recorded in detail and showing the event rate in 90 days of each treatment group in summary statement.

The event rate for each treatment group will be calculated as: the sum of number of event for all the patients / the sum of number of treatment periods for all the patients.

## Time to Event Analysis

Differences between treatments in the risk of new stroke (ischemic or hemorrhagic) event and combined vascular events during maximum 90-day follow-up were assessed using standard Kaplan-Meier time-to-event approaches. The time to the first event was used in the model when there were multiple events of the same type. Patients were considered censored at the time of study termination or death if there were no events occurred during the study.

# 11.Study Population

## Disposition of Subjects

The number of subjects in each analysis population will be presented, subjects to be excluded from the Per Protocol population will be listed, and the total number of subjects attending each clinic visit will also be summarized by treatment group.

The number of subjects randomized, completed and prematurely withdrawn from the study will be presented for each treatment group. The primary reasons for withdrawal both prior to and post randomization will also be presented.

A data display listing and summary of deviations from the inclusion/exclusion criteria will be presented for all subjects who were either entered or randomized into the trial.

### Protocol Deviations

Subject data will be examined for evidence of protocol violators in order to assess how well the protocol was followed. Inclusion and exclusion criteria are detailed in the study protocol.

Subjects who commit protocol violations will be included in the FAS Population but excluded from the Per Protocol Population. These protocol violations will be shown in a listing. Subjects can either be full or partial protocol violators. A full protocol violator is completely excluded from the Per Protocol Population. A partial protocol violator has only some data excluded. For subjects who violated the protocol during the treatment period due to unpermitted changes in the medication or prohibited concurrent medication, the analysis will only use data recorded prior to the violation. For all violations which reference the treatment period, the treatment start date will be used as the reference date.

A listing of all possible protocol violators will be produced for clinical review. The final list of subjects who are protocol violators and are therefore excluded from the Per-Protocol population will be agreed by the study team.

### Demographic and Baseline Characteristics

The following demographic information will be listed and summarized for subjects in each treatment group: age, sex, body mass index (BMI). This will also be done for stroke and TIA history, medical history, smoking history, alcohol use, symptoms of the index event, pretreatment Rankin Score and NIHSS score.

Vital signs including supine systolic blood pressure, diastolic blood pressure, and heart rate will also be listed and summarized in each treatment group.

The continuous data followed normal distribution will be presented as mean and standard deviation, and the continuous data followed skewness distribution will be presented as median and

interquartile range; categorical data will be presented as n(%). T-test or Wilcoxon rank sum test will be used for comparison between two continuous data, and Chi-squared tests, Fisher exact test, or Wilcoxon rank sum test will be used for comparison between two categorical data.

## **12.Efficacy Analyses**

### **Primary Efficacy Analysis**

The primary endpoint is the rate of new stroke (both ischemic and hemorrhagic) reported during the 3 months treatment period. FAS will be the primary population for efficacy analyses. PPS will be used as secondary population for the efficacy analyses. If the results in the PPS population are inconsistent with the FAS population, detailed analysis of the inconsistent results is required.

#### **Main Model**

The time to first new stroke (both ischemic and hemorrhagic) reported during the 3 months treatment period for the FAS Population will be summarized by treatment group using Kaplan-Meier estimates. The hazard ratio for the treatment comparison will be derived using a Cox proportional hazards model, including the pooled study center as a random effect. The hazards ratios with 95% CI will be reported. This will also be presented graphically on a Kaplan-Meier curve. The log-rank test will be used to evaluate the statistical significance of the treatment effect.

#### **Interactions with Subgroups**

Summary tables will be produced for the predefined subgroups and interactions between treatment and these subgroups will be investigated, using a Cox proportional hazards model. A separate model will be used for each interaction to determine its significance. This will also be presented graphically on a forest plot.

The predefined subgroups including:

Version 1.0

Jan 09 2019

- Gender (male vs. female)
- Different age category (<65 years vs. ≥65 years)
- Etiological stroke subtype (main subgroups type of ischemic stroke)
- History of diabetes (yes vs. no)
- CYP2C19 genetic variants (intermediate metabolizers vs. weak metabolizers)
- Target event (TIA vs. mild stroke)
- Responsible blood vessels (Intracranial artery stenosis vs. extracranial arterial stenosis)

### Secondary Efficacy Analyses

#### **Rate of new clinical vascular events (any stroke, TIA, myocardial infarction, or vascular death) and the individually event within 3 months**

The rate of new clinical vascular events occurring within 3 months will be analyzed using a Cox proportional hazard model similar to that in the previous section, with the pooled study center as a random effect. A combined vascular event is defined as any of the 4 following events: stroke, TIA, myocardial infarction, or vascular death. This will also be presented graphically on a Kaplan-Meier curve. Each of the 4 vascular events will also be analyzed using the same method and the event rate for each event will be calculated for each treatment group. The hazard ratios with 95% CIs will be reported. The log-rank test will be used to evaluate the statistical significance of the treatment effect.

#### **Rate of new ischemic stroke within 3 months**

The rate of ischemic stroke occurring within 3 months will be analyzed using a Cox proportional hazard model, with the pooled study center as a random effect. This will also be presented graphically on a Kaplan-Meier curve. The hazard ratio with 95% CI will be reported. The log-rank test will be used to evaluate the statistical significance of the treatment effect.

**Modified Rankin Scale score dichotomized at percentage with score 0-2 vs 3-6 at 3 months follow up**

Logistic regression will be performed to compare proportion of Modified Rankin Scale score 0-2 vs 3-6 at 3 months follow-up between the two treatment groups. The odds ratio with 95% CI will be reported.

**Neurological impairment at 3 months follow-up**

Changes of NIHSS scores between the end of study and baseline will be summarized for the two treatment groups among the survivors during the study. The treatment difference will be tested using student t-test or Wilcoxon rank sum test as appropriate.

**Quality of life at 3 months follow-up**

Health related quality of life will be measured using EuroQol EQ-5D scale among the survivors. Treatment differences will be tested using student t-test or Wilcoxon rank sum test as appropriate.

**Rate of any new strokes (ischemic stroke or hemorrhagic stroke) within 1 year**

The rate of new stroke (both ischemic and hemorrhagic) reported within 1 year will be analyzed using a Cox proportional hazard model, with the pooled study center as a random effect. This will also be presented graphically on a Kaplan-Meier curve. The hazard ratio with 95% CI will be reported. The log-rank test will be used to evaluate the statistical significance of the treatment effect.

**Rate of new clinical vascular events (any stroke, TIA, myocardial infarction, or vascular death) and the individually event within 1 year**

The rate of new clinical vascular events occurring within 1 year will be analyzed using a Cox proportional hazard model, with the pooled study center as a random effect. A combined vascular event is defined as any of the 4 following events: stroke, TIA, myocardial infarction, or vascular death. This will also be presented graphically on a Kaplan-Meier curve. Each of the 4 vascular events will also be analyzed using the same method and the event rate for each event will be calculated for each treatment group.

The hazard ratios with 95% CIs will be reported. The log-rank test will be used to evaluate the statistical significance of the treatment effect.

#### **Rate of new ischemic stroke within 1 year**

The rate of ischemic stroke occurring within 1 year will be analyzed using a Cox proportional hazard model, with the pooled study center as a random effect. This will also be presented graphically on a Kaplan-Meier curve. The hazard ratio with 95% CI will be reported. The log-rank test will be used to evaluate the statistical significance of the treatment effect.

#### **Modified Rankin Scale score dichotomized at percentage with score 0-2 vs 3-6 at 1-year follow up**

Logistic regression will be performed to compare proportion of Modified Rankin Scale score 0-2 vs 3-6 at 1-year follow-up between the two treatment groups. The odds ratio with 95% CI will be reported.

#### **Neurological impairment at 1-year follow-up**

Changes of NIHSS scores between the end of study and baseline will be summarized for the two treatment groups among the survivors during the study. The treatment difference will be tested using student t-test or Wilcoxon rank sum test as appropriate.

#### **Quality of life at 1-year follow-up**

Health related quality of life will be measured using EuroQol EQ-5D scale among the survivors. Treatment differences will be tested using student t-test or Wilcoxon rank sum test as appropriate.

### **13.Safety Analyses**

All analyses of safety data will be carried out using the safety set (SS) population.

#### **Extent of Exposure**

The extent of exposure will be calculated as the number of days between start of treatment and end of treatment (i.e. treatment stop date – treatment start date + 1), and

categorized into months: <1, 1–2, 2–3 months. Exposure will then be summarized by treatment group.

### **Bleeding Events**

Severe or moderate bleeding (GUSTO definition) within 3 months;

Severe or moderate bleeding (GUSTO definition) at 1 year;

Any bleeding events (severe or moderate hemorrhage, intracranial hemorrhage) within 3 months and 1 year;

Symptomatic and asymptomatic intracranial hemorrhagic events within 3 months and 1 year;

For most bleeding events, the Cox proportional hazards model will be used to compare the hazard ratio (HR) between the two treatments, or Poisson regression or negative binomial regression which are more appropriate for the analysis of rare event.

### **Adverse Events**

Adverse events (AEs) will be coded using the MedDRA coding dictionary (Version 6.0 or a later release) and grouped by system organ class (as detailed in the study protocol). Separate data display listings and summaries will be presented for adverse events that start prior to first dose of study medication (pre-treatment), whilst on study medication (during treatment) and after the last dose of study medication (post-treatment).

Within each treatment group, the number and percentage of subjects experiencing an AE will be summarized by system organ class and preferred term and Fisher's Exact test will be used to compare the number of each grouped AE event between treatment groups. In addition, a separate summary will be provided for AEs experienced by more than 5% of subjects in either of the treatment groups.

### **Deaths and Serious Adverse Events**

Summary tables and data displays will be provided for serious adverse events (as detailed in the study protocol). In addition, all deaths and serious AE's will be documented in a case narrative format in the clinical study report.

The number of deaths occurring over the treatment period will be summarized and Fisher's Exact test will be used to compare the number of deaths between treatment groups.

## 1. Introduction

This statistical analysis plan (SAP) documents the planned statistical analyses for the CHANCE-2 study and is based on the protocol, together with any subsequent amendments.

This SAP is intended for the use of project team members and should be read in conjunction with the aforementioned protocol.

## 2. Study Objective

The primary objective of the study is to assess the effects of ticagrelor plus aspirin versus clopidogrel plus aspirin on reducing the 3-month risk of any new stroke (ischemic or hemorrhagic, primary outcome) when initiated within 24 hours of symptom onset in *CYP2Y19* LOF alleles carriers with TIA or minor ischemic stroke.

The secondary objectives of the study are:

- 1) To assess the different rate of composite vascular outcome: composite of any stroke, TIA, myocardial infarction, and vascular death at 3-month and at one-year;
- 2) To assess the effects of ticagrelor plus aspirin regimen versus clopidogrel plus aspirin regimen on the incidence of: stroke within 30 days, neurological impairment at 3 months (NIHSS increased  $\geq 4$  from baseline), ischemic stroke, TIA, MI, vascular death, disabling stroke (mRS: 2-6) at 3-month and at one-year;
- 3) To assess the incidence and severity of recurrent stroke and TIA during follow-up to 3 months and 1-year (Severity is measured using a six-level ordered categorical scale that incorporates the mRS: fatal stroke/severe non-fatal stroke [mRS 4 or 5]/moderate stroke [mRS 2 or 3]/mild stroke [mRS 0 or 1]/TIA/no stroke-TIA);
- 4) To compare the safety of the two treatment regimens in terms of:

- Severe or moderate bleeding (GUSTO definition)
- Bleeding events
- Total mortality
- Adverse events/ Severe adverse events

5) To evaluate Quality of Life (EuroQol EQ-5D scale) among survivors;

6) Subgroup analyses: The primary efficacy endpoint will also be analyzed stratified by age (<65 vs. ≥65 years), gender (men vs. women), Body Mass Index (BMI), index event (TIA vs. Minor stroke), time from index event to randomization, etiology subtype, diabetes mellitus, hypertension, type of LOF allele, previous ischemic stroke or TIA, prior antiplatelet therapy, prior statin therapy, prior smoking status, and symptomatic intracranial and extracranial artery stenosis will be evaluated in subgroup analyses.

### **3. Study Endpoint(s)**

#### **Primary Efficacy Endpoints:**

Any new stroke events (ischemic stroke or hemorrhagic stroke) within 3 months.

#### **Secondary Efficacy Endpoint:**

- 1) Any new stroke events (ischemic stroke or hemorrhagic stroke) within 30 days and 1 year;
- 2) New clinical vascular events (ischemic stroke/ hemorrhagic stroke/ TIA/ MI/ vascular death) within the 3 months and 1 year;
- 3) New ischemic stroke within 3 months and 1 year;
- 4) Disabling stroke (Modified Rankin Scale score, mRS>1) at 3 months and 1 year;
- 5) Incidence and severity of recurrent stroke and TIA during follow-up to 3 months and

1-year (Severity is measured using a six-level ordered categorical scale that incorporates the mRS: fatal stroke/severe non-fatal stroke [mRS 4 or 5]/moderate stroke [mRS 2 or 3]/mild stroke [mRS 0 or 1])/TIA/no stroke-TIA);

6) Neurological impairment at 3 months (NIHSS increased  $\geq 4$  from baseline);

7) Quality of Life (EuroQol EQ-5D scale) at 3 months and at 1 year.

### Primary Safety Endpoint

Incidence of severe bleedings or moderate bleedings (GUSTO definition) at 3 months.

### Secondary Safety Endpoint

1) Incidence of severe bleedings or moderate bleedings (GUSTO definition) at 1 year;

2) Bleeding events (severe or moderate bleedings or intracranial hemorrhage) at 3 months and 1 year;

3) Mortality within 3 months and 1 year;

4) AEs/SAEs reported by the investigators at 3 months and 1 year.

## 4. Statistical Hypotheses

The primary endpoint for this study is new stroke event (ischemic stroke or hemorrhagic stroke) within the 3-month treatment period. In this study of patients with TIA or MIS carried CYP2C19 LOF allele treated with aspirin 75 mg/d, the null hypothesis of no difference in 90-day risk of new stroke between the two treatment groups will be tested using a two-sided test at the 5% level of significance.

$$H_0: \lambda_1/\lambda_2=1$$

$$H_1: \lambda_1/\lambda_2 \neq 1$$

Where  $\lambda_1$  is the rate of new stroke over the 3-month treatment period in the group treated with ticagrelor plus aspirin regimen and  $\lambda_2$  is the same endpoint in the group

treated with clopidogrel plus aspirin regimen.

## 5. Design

The CHANCE-2 study is a multicenter, double-blind, placebo-controlled, randomized clinical trial. Patients with acute nondisabling cerebrovascular events, including acute minor stroke and transient ischemic attack (TIA), are at high risk of recurrent stroke and cardiovascular events. The objective of the CHANCE-2 study is to assess the effects of ticagrelor plus aspirin versus clopidogrel plus aspirin on reducing the 3-month risk of any stroke (both ischemic and hemorrhagic, primary outcome) when initiated within 24 hours of symptom onset in *CYP2C19* LOF alleles carriers with TIA or minor stroke. Eligibility criteria for the trial participants include 40 years of age or older, *CYP2C19* LOF alleles carriers with high-risk TIAs, defined as an ABCD2 score  $\geq 4$ , or acute non-disabling ischemic stroke, with a National Institutes of Health Stroke Scale (NIHSS) score  $\leq 3$ , and can be treated with study drug within 24 h after symptoms onset. Patients with diagnosis of hemorrhage or other pathology, contraindication to ticagrelor, clopidogrel or ASA, clear indication for anticoagulation, or intravenous thrombolytic therapy (such as intravenous rtPA) or mechanical thrombectomy will be excluded. In this study a novel point-of-care genetic test platform was used to identify carriers of the *CYP2C19* LOF alleles including poor metabolizers with at least two \*2 or \*3 alleles (\*2/\*2, \*2/\*3, or \*3/\*3) or intermediate metabolizers with one \*2 or \*3 allele (\*1/\*2 or \*1/\*3). All eligible patients will be randomized to receive either the ticagrelor plus aspirin group or the clopidogrel plus aspirin group. Patients in the ticagrelor plus aspirin group will receive ticagrelor of loading dosing of 180mg followed by 90mg bid for 3 months plus aspirin of loading dose of 75-300mg followed by 75mg daily for 21 days. Patients in clopidogrel plus aspirin group will receive clopidogrel of loading dosing of 300mg followed by 75mg daily for 3 months plus aspirin loading dose of 75-300mg followed by 75mg daily for 21 days. The study drug should be initiated as soon as

possible within 24 hours of symptoms onset. The primary efficacy outcome is any new stroke (ischemic or hemorrhage) within 3 months. Secondary outcomes include any new stroke within 30 days and 1 year, following event within a 3 months and 1 year timeframe: (1) new clinical vascular events including ischemic stroke, hemorrhagic stroke, TIA, myocardial infarction, and vascular deaths; (2) Ischemic stroke; (3) Disabling stroke (Modified Rankin Scale score, mRS>1); (4) Incidence and severity of recurrent stroke and TIA; (5) Quality of Life (EuroQol EQ-5D scale; and Neurological impairment at 3 months (NIHSS increased  $\geq 4$  from baseline). The primary safety outcome was incidence of severe bleedings or moderate bleedings event at 3 months, according to the Global Utilization of Streptokinase and Tissue Plasminogen Activator for Occluded Coronary Arteries (GUSTO) definition. The trial was approved by the ethics committee of the participating hospitals. The study was registered with ClinicalTrials.gov (NCT04078737).

### ***Planned Analyses***

The analyses that are detailed in this SAP will be performed only when the database has been locked, all protocol violators identified, and treatment allocations have been unblinded. Membership of the Full Analysis and Per Protocol populations will be determined using the rules set out in this SAP. At a date to be agreed within the project team, a data look will be performed. This will involve production of all data displays on a subset of the data using dummy treatment codes. These are produced purely as an aide to the pre-programming of the study and no unblinding will occur.

### ***Interim Analyses***

Data and Safety Monitoring Board (DSMB) is in place to ensure the safety of subjects in the study. An independent statistician will prepare summary statistics on enrollment, subject status in the study, baseline characteristics, and safety data, including summary tables of coded SAEs and these will be examined by the DSMB. These tables will be provided to the DSMB at regular intervals. If the tables give rise to safety concerns for

any treatment, the DSMB may recommend that the trial should be modified or stopped prematurely. The Steering Committee will, in conjunction with the sponsor, decide whether to act on this recommendation.

The interim analysis is based on the stopping boundaries calculated by the Lan-DeMets method with an O'Brien-Fleming type alpha spending function. One interim and one final analysis are planned to be conducted. We planned one interim analysis when 60% of total patients had undergone randomization and completed follow-up. Let  $p_0$  and  $p_1$  be the proportion of primary outcome (new stroke) for the control and intervention group respectively. Let  $d = p_0 - p_1$  and  $\hat{d}$  be the observed difference. The following table lists the stopping boundaries for the interim analysis.

Table. Interim analysis for testing  $H_0: d=0$  vs  $H_a: d \neq 0$

| Stage | Expected sample size* | Boundary value | Rule                                                                                    | Type I error achieved |
|-------|-----------------------|----------------|-----------------------------------------------------------------------------------------|-----------------------|
| 1     | 3838                  | 0.035          | If $ \hat{d}  > 0.035$ , reject $H_0$ and stop;
otherwise continue to the next stage | 0.008                 |
| 2     | 6396                  | 0.023          | If $ \hat{d}  > 0.023$ , reject $H_0$ and stop;
otherwise stop, accept $H_0$         | 0.048                 |

Note: \* indicates the sample size is adjusted for 5% of loss of follow-up over 3 months

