## 7.2 Randomization of the *CYP2C19* intermediate/poor metabolizers

The list of randomization code ~~list~~ will be generated centrally by a Contract

Research Organization (CRO).

The patient kits will be packaged in accordance with this randomization code list. During the treatment period, the patient will receive study medication according to the corresponding group, either the ticagrelor plus ASA group or the clopidogrel plus ASA group, using a randomization ratio of 1:1.

The treatment number will be allocated using a centralized treatment allocation system on D1 (baseline visit). Subjects will be randomly assigned into groups, from small to large, to obtain the treatment number. According to this number, the investigator will give the first box of the corresponding package to the patient. Based on the progress of each center, the goal of enrollment can be adjusted, but it needs to be confirmed by the data management committee.

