## 6. Sample size estimates

The study hypothesized that there is no difference in 90-day risk of stroke (ischemic or hemorrhagic) in those treated with a 3-month regimen of ticagrelor initiated with a loading dose of 180 mg followed by 90 mg bid compared with a 3-month regimen of clopidogrel initiated with a loading dose of 300 mg followed by 75 mg/d when therapy is initiated within 24 hours of symptom onset in patients with TIA or minor ischemic

stroke carried *CYP2C19* LOF allele treated with aspirin 75 mg/d.

The minimum necessary sample size in the trial is established by the requirement to detect the smallest expected, clinically meaningful treatment difference comparing the treatment with placebo. Based on the genetic sub-analysis of the CHANCE study, we presume that the 90-day risk of stroke recurrence in *CYP2C19* loss-of-function allele carriers is about 9.4%, and 6.7% for noncarriers. With the point-of-care identification of the *CYP2C19* loss-of-function allele carriers to assess a proper pharmacogenetic approach for patients with high-risk TIA or MIS, we assumed a 25% relative risk reduction with alteration from clopidogrel to ticagrelor (90-day risk of stroke recurrence: 7.1%). Considering the potential impact of the interim analyses on the probability of type I error, we adjusted the statistical significance to a 2-sided  $\alpha$  of 0.048. With a sample size of 6,396 patients, we will have 90% power to detect a relative risk reduction (Ticagrelor: loading dose: 180mg, 90mg bid on day 2-90 vs. Clopidogrel: loading dose: 300mg, 75mg qd on day 2-90) of 25% and 5% dropouts (medication nonadherence). Assuming 58.8% prevalence of *CYP2C19* loss-of-function allele carriers in a Chinese population, we projected screening 10,878 patients would be necessary. Based on the results of interim analysis, the DSMB will recommend whether the sample size need to be re-calculated.

According to the DSMB meeting on April 7, 2021, the DSMB lookup the overall event rates of the trial and suggested not to unblind the treatment assignment in the interim analysis. Therefore, comparison of efficacy and safety outcome between two treatment groups were not performed in the interim analysis, and sample size was not re-calculated. The type I error level of the statistical significance will be set to a 2-sided  $\alpha$  of 0.05 in the final analysis.

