### **Main Model**

The time to first new stroke (ischemic stroke or hemorrhagic stroke) reported during the 3 months treatment period for the FAS Population will be summarized by treatment group using Kaplan-Meier estimates. The hazard ratio for the treatment comparison will be derived using a Cox proportional hazards model, including the pooled study center as a random effect. The hazards ratios with 95% CI will be reported. This will also be presented graphically on a Kaplan-Meier curve. The log-rank test will be used

to evaluate the statistical significance of the treatment effect.

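### The SAP's stopping table sets risk-difference cut-offs (0.035 interim, 0.023 final) that do not match its stated error rates; the final cut-off equals the design effect, so that rule has about 50% power, not 90%

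*Supplement*

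**What the plan says.** SAP version 1.3, section 5 (Interim Analyses), tabulates two stages on the scale of the observed difference in stroke proportions.

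- **Stage 1** (3,838 patients): reject if the absolute difference exceeds 0.035, otherwise continue. Type I error is given as 0.008.
- **Stage 2** (6,396 patients): the cut-off and its consequence read "0.023$ , reject $H_0$ and stop; otherwise stop, accept $H_0". Type I error is given as 0.048.

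The footnote "indicates the sample size is adjusted for 5% of loss of follow-up over 3 months" applies to both sample sizes.

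SAP section 6 takes the control risk from the statement that risk in "loss-of-function allele carriers is about 9.4%, and 6.7% for noncarriers". It assumes a 25% "relative risk reduction with alteration from clopidogrel to ticagrelor (90-day risk of stroke recurrence: 7.1" percent) and says "With a sample size of 6,396 patients, we will have 90% power to detect a relative risk reduction" of that size. It then reports that no between-group comparison was made at the interim and sets the final two-sided alpha to 0.05. The table was not changed to match.

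SAP section 12 (Main Model) analyses time to first stroke: "The hazard ratio for the treatment comparison will be derived using a Cox proportional hazards model", and the log-rank test decides significance. Sections 4 and 9 also work at the 5% level. Protocol version 1.4, section 13.4, expresses the two looks as P-value thresholds of 0.008 and 0.048.

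**The concern.** A boundary on the difference scale should be the critical z value times the standard error of the difference. The stage 2 value of 0.023 is instead 9.4% minus 7.1%, the effect used to size the trial. A rule that rejects only when the estimate exceeds the assumed true effect succeeds about half the time when that effect is real, whatever the sample size.

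If the table is followed, any final difference between about 0.014 and 0.023 leads to acceptance of the null although it is significant at the stated level. The log-rank rule in section 12 would call the same results positive. The primary conclusion for results in that range would then depend on which part of the SAP is applied, and that choice could be made after unblinding.

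**Working it through.** **Inputs.** Control risk p0 = 0.094, intervention risk p1 = 0.071, power 90%, N = 6,396 (SAP section 6). Loss of 5% and the interim at 60%, 3,838 patients (SAP section 5). Equal allocation (protocol section 7.2, "using a randomization ratio of 1:1"). Two-sided alphas 0.008 and 0.048 (protocol section 13.4 and the SAP table). Pooled risk = (0.094 + 0.071)/2 = 0.0825.

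**1. Reproduce the plan's sample size.**

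n per arm = [z(α/2)·√(2·p̄(1−p̄)) + z(β)·√(p0(1−p0) + p1(1−p1))]² / (p0−p1)²

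- First term: 1.977 × √(2 × 0.0825 × 0.9175) = 0.7694
- Second term: 1.282 × √(0.094 × 0.906 + 0.071 × 0.929) = 0.4982
- n = (1.2676)² / 0.023² = 3,038 per arm, 6,076 in total
- 6,076 / 0.95 = 6,396, an exact match

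**2. Reproduce the alphas.** Lan-DeMets O'Brien-Fleming spending of 0.05 at information fraction 0.6 gives nominal two-sided levels of 0.0076 (z = 2.669) and 0.0476 (z = 1.981). These round to the stated 0.008 and 0.048.

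**3. What the tabulated cut-offs imply.** Under the null, SE = √(4 × 0.0825 × 0.9175 / N). The evaluable numbers are the planned numbers less 5%.

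| Look | N | SE | Cut-off | z | Two-sided P | Stated |
|---|---|---|---|---|---|---|
| Interim | 3,838 | 0.00888 | 0.035 | 3.94 | 0.00008 | 0.008 |
| Interim, evaluable | 3,646 | 0.00911 | 0.035 | 3.84 | 0.00012 | 0.008 |
| Final | 6,396 | 0.00688 | 0.023 | 3.34 | 0.0008 | 0.048 |
| Final, evaluable | 6,076 | 0.00706 | 0.023 | 3.26 | 0.0011 | 0.048 |

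With both arms at 9.4%, the P values are 0.0002 to 0.0003 (interim) and 0.0016 to 0.0021 (final). To reach the stated alphas, the pooled risk would have to be about 20 to 21% for the interim row and 29 to 32% for the final row, so no single event rate explains both.

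**4. Boundaries that match.**

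- Interim: 2.669 × 0.00888 = 0.0237 (0.0243 on 3,646)
- Final: 1.981 × 0.00688 = 0.0136 (0.0140 on 6,076)
- Final at alpha 0.05: 1.960 × 0.00688 = 0.0135 (0.0138 on 6,076)

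**5. Power of the final rule.** Power = 1 − Φ[(cut-off − true difference)/SE₁], where SE₁ = √(2·[p0(1−p0) + p1(1−p1)]/N) = 0.00687 at 6,396.

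- Cut-off 0.023, true difference 0.023: 1 − Φ(0) = 50%
- Cut-off 0.023, exactly 25% reduction (p1 = 7.05%, difference 0.0235): 53%
- A cut-off anywhere from 0.0225 to 0.0235 (rounding) gives 47% to 56% across the two values of p1
- Cut-off at the matching value of about 0.014: 90.0% on 6,076 and 91.4% on 6,396

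Adding the interim look moves the 50% only to 50.2%. At the interim, the chance of crossing 0.035 at the design effect is about 9%; at 0.0237 it is about 47% (both on 3,838).

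**6. An example of the conflict.** Observed risks of 9.4% and 7.4% (pooled 8.4%) differ by 0.020. On 6,396, z = 0.020 / √(4 × 0.084 × 0.916 / 6,396) = 2.88, P = 0.004 (0.005 on 6,076). The table says accept the null.

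**The case against.** The strongest reply is that the table no longer governs anything. It sits under the interim heading. SAP section 6 records that no between-group interim comparison took place and resets the final alpha to 0.05. Sections 4, 9 and 12 all decide the primary endpoint by a P value, and section 12 names the log-rank test. On that reading power stays near 90%, and the 50% belongs to a leftover row. A difference-scale boundary is also not wrong in kind: over 90 days with little censoring, the log-rank test is close to a comparison of two proportions, so such a boundary can be a translation of the P-value threshold.

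Much of this stands. The interim row has no remaining practical effect, the 50% applies only if the table's rule is followed, and the fault lies in the values rather than in the scale.

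It does not dispose of the point. Stage 2 is the final analysis, not an interim look. Its row gives an explicit reject-or-accept rule for the primary endpoint and remains in the April 2021 SAP. Nothing in the SAP says that section 12 overrides it.

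**Conclusion.** The point holds. The tabulated cut-offs do not deliver the error rates beside them: the final one corresponds to P of about 0.001 to 0.002 rather than 0.048, and the interim one to about 0.0001 to 0.0003 rather than 0.008. These ranges cover planned and evaluable numbers and pooled risks of 8.25% and 9.4%. Applied literally, the final rule has 50% power at a true difference of 0.023 and 53% at exactly a 25% reduction, against the stated 90%.

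The sample size of 6,396 and the P-value thresholds are correct, and the planned power is roughly preserved if the log-rank test at 0.05 decides. That last statement uses the two-proportion approximation to the log-rank test. The defect is a wrong decision threshold for the primary endpoint, left beside a conflicting correct one. It should be corrected before unblinding.

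**What to change.** Delete the risk-difference thresholds from the table in SAP section 5, and with them the instruction to accept the null. State once that the primary conclusion rests on the two-sided log-rank P value against a single final alpha, 0.05 under SAP section 6, and that no other rule applies.

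If difference-scale values are kept for illustration, label them as approximate and conditional on a pooled risk of 8.25%, and correct them to about 0.024 at the interim (z = 2.67) and about 0.014 at the final analysis (z = 1.96 to 1.98). Note beside the interim row that the comparison was not carried out.

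The cost is SAP wording only. Sample size, data collection and the planned primary test do not change.
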